##### Ambulatory Home Care Record-Hybrid (AHCR-hybrid)

In addition to the AHCR [27], a hybrid form was developed with a set of customized study-specific questions [28] which was appended to better capture the data needs of the planned economic evaluation. We will use the AHCR-hybrid to collect health care resource utilization. Completed monthly, it will be used to capture public and private healthcare utilization including ED visits, hospitalizations, ambulatory/out-patient, and home-based health services. The tool will also capture patient and caregiver private and out-of-pocket health care expenditures, lost productivity relating to caregiving or obtaining medical care as well as adverse events or performance issues related to the use of aTouchAway™ platform and the internet.

Intervention costs for the technology, the aTouchAway^TM^ platform, will be obtained from commercial pricing as well as study data. Both implementation and annual maintenance costs for the intervention will be determined on a per-patient basis and assigned to each participant in the intervention arm.

#### Participant and caregiver experience measures

These will be collected via telephone by a blinded Research Coordinator.

##### Pearlin Self-Mastery Scale

The Pearlin Mastery Scale (PM) measures an individual’s sense and level of mastery. Mastery is a psychological resource defined as “the extent to which one regards one’s life-chances as being under one’s own control in contrast to being fatalistically ruled,” [29]. The 7-item scale comprises five negatively worded items and two positively worded items, presented with the following response options: (1) strongly disagree, (2) disagree, (3) agree, (4) strongly agree. The negatively worded items require reverse coding prior to scoring, resulting in a score range of 7 to 28, with higher scores indicating greater levels of mastery [29]. Caregiver reported Pearlin-Self Mastery Scale was chosen as the co-primary outcome over the self-reported Pearlin-Self-Mastery Scale as not all study participants would be able to complete a self-reported questionnaire. Caregiver reported and participant reported Pearlin Self-Mastery Scales will both be obtained where possible.

##### Zarit Burden Interview (ZBI)

We will use this 22-item questionnaire to assess caregiver burden (change from baseline to 6 and 12 months). The 22 items are assessed on a 5-point Likert scale, ranging from 0 = “never” to 4 = “nearly always.” The questions focus on areas such as caregiver health, psychological well-being, finances, social life, and the relationship between them and their family member (study participant). This questionnaire has demonstrated validity and reliability in caregivers of individuals with chronic conditions [30, 31].

##### Euro-Quality of Life- 5 Dimensions Scale (EQ-5D)

The EQ-5D is a well-known and widely used health status instrument. It provides a concise, generic instrument used to measure, compare, and value health status across disease areas [32, 33]. The instrument provides a health utility score. We will use the EQ-5D-5L (above 18 years of age) and EQ-5D Youth (EQ-5DY) (pediatrics; 4–18 years of age) to assess VAI health status (change from baseline to 6 and 12 months). The EQ-5D will also be used in the cost-utility analysis to observe change between the two groups. The utility score will be used in the calculation of the incremental cost-effectiveness ratio [34].

##### Family Experiences with Coordination of Care (FECC)

We will use the FECC to assess the family perception of the quality of care coordination. This questionnaire has demonstrated validity and reliability in individuals with medical complexity [35]. The FECC will be administered to study participants and family caregivers participating in the qualitative interviews along with other questions that explore experiences with care coordination.

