**Objectives and brief methods:**

Our primary objective is to evaluate the TtLIVE intervention compared to a usual care control group using an eight-center, pragmatic, parallel-group single-blind (outcome assessors) randomized controlled trial. Eligible patients are children and adults newly transitioning to HMV in Ontario, Canada. Our target sample size is 440 participants (220 each arm). Our co-primary outcomes are a number of emergency department (ED) visits in the 12 months after randomization and change in family caregiver (FC) reported Pearlin Mastery Scale score from baseline to 12 months. Secondary outcomes also measured in the 12 months post randomization include healthcare utilization measured using a hybrid Ambulatory Home Care Record (AHCR-hybrid), FC burden using the Zarit Burden Interview, and health-related quality of life using the EQ-5D. In addition, we will conduct a cost-utility analysis over a 1-year time horizon and measure process outcomes including healthcare provider time using the Care Coordination Measurement Tool. We will use qualitative interviews in a subset of study participants to understand acceptability, barriers, and facilitators to the TtLIVE intervention. We will administer the Family Experiences with Care Coordination (FECC) to interview participants. We will use Poisson regression for a number of ED visits at 12 months. We will use linear regression for the Pearlin Mastery scale score at 12 months. We will adjust for the baseline score to estimate the effect of the intervention on the primary outcomes. Analysis of secondary outcomes will employ regression, causal, and linear mixed modeling. Primary analysis will follow intention-to-treat principles. We have Research Ethics Board approval from SickKids, Children’s Hospital Eastern Ontario, McMaster Children’s Hospital, Children’s Hospital-London Health Sciences, Sunnybrook Hospital, London Health Sciences, West Park Healthcare Centre, and Ottawa Hospital.

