#### Nested qualitative interviews

We will conduct semi-structured interviews with a purposive diverse sample (ALS versus non-ALS, invasive versus non-invasive ventilation, different study sites, rural versus urban residence, low (< 40%) and high (≥70%) intervention adherence) of 20 VAIs, 20 family caregivers of study participants and 20 circle of care healthcare providers (at 6 months (*n*=60)) to explore barriers and facilitators to intervention adherence.

To participate in interviews, participants or their caregivers must be able to communicate verbally for the duration of an interview. Health care providers must meet the following criteria:

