**Healthcare providers**								
Care Coordination Measurement Tool	< 5 min				X			
Qualitative interviews**	60 min						X	X

***Only completed by intervention group

**Only completed by a subset of participants/ caregivers/ healthcare providers

*Only completed by caregivers completing qualitative interviews

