## Statistical methods

### Statistical methods for primary and secondary outcomes {20a}

The number of ED visits will be analyzed using Poisson or negative binomial regression. Pearlin Mastery Scale scores at 12 months will be analyzed using linear or robust regression models depending on the distribution of the data and adjusting for baseline Pearlin score. Both analyses will adjust for the for the stratified clinical site. We will conduct a secondary analysis of the primary outcome, ED visits, adjusting for a priori chosen clinically important covariates: age, sex, and clinical site; and stratified by pediatric, adult ALS, and adult non-ALS and ventilation type (invasive or non-invasive ventilation). Analysis of secondary outcomes, viewed as exploratory in nature, will vary depending on the outcome: count data (i.e., number of hospitalizations) will be compared with Poisson or negative binomial regression as appropriate; hospital free survival via Kaplan- Meier curves and Cox proportional hazards; time to ED admission and hospitalization using Fine and Gray models to account for competing risk of death; continuous repeated measures outcomes (EQ-5D-3L/5D-Y, FECC, ZBI, and CCMT) using linear mixed effects models.

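### FECC is listed for linear mixed models with the trial outcomes, but it is collected only in a purposive interview sample chosen partly on adherence, so an arm comparison of it would not be randomised

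*Protocol article*

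**What the plan says.** **Who gets FECC.** The FECC section states: "The FECC will be administered to study participants and family caregivers participating in the qualitative interviews". The abstract agrees: "We will administer the Family Experiences with Care Coordination (FECC) to interview participants". Table 5 places FECC under caregivers at 6 and 12 months with no baseline, and one of its footnotes, most naturally the one for this row, reads "Only completed by caregivers completing qualitative interviews".

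**How interviewees are chosen.** Nested qualitative interviews: "We will conduct semi-structured interviews with a purposive diverse sample", made up of "20 VAIs, 20 family caregivers of study participants and 20 circle of care healthcare providers (at 6 months"). One of the five diversity criteria is "low (< 40%) and high (≥70%) intervention adherence". The stated purpose is to learn what helps or hinders adherence to the intervention. Under Process measures, adherence is recorded only for participants randomised to TtLIVE.

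**How FECC is analysed.** Section {20a} assigns "continuous repeated measures outcomes (EQ-5D-3L/5D-Y, FECC, ZBI, and CCMT) using linear mixed effects models". The same sentence opens: "Analysis of secondary outcomes, viewed as exploratory in nature, will vary depending on the outcome". FECC carries no subset restriction there.

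**Status of FECC.** Objectives {7} and Table 4 class it as a process measure, not a secondary outcome.

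**The concern.** Section {20a} sets out how the outcomes of a two-arm trial are to be analysed. A model listed there is naturally read as estimating the effect of allocation. For FECC, the people who supply data are not the randomised groups, nor a random sample of them. They are picked by the study team, partly on how well they used the intervention, and use of the intervention can be known only after randomisation and only in one arm.

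At stake is whether a FECC difference between arms could be reported beside EQ-5D and Zarit results as though it had the same standing. FECC is the trial's family-reported scale of coordination quality and bears on the patient and family experience domain in the Objectives. Neither co-primary outcome is touched.

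**Working it through.** **1. The sections side by side**

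| Measure in the {20a} list | Who supplies data | Arms comparable by design? |
|---|---|---|
| EQ-5D | Planned trial-wide (adult and youth versions, from age 4) | Yes |
| Zarit interview | Planned for all caregivers | Yes |
| CCMT | Random 10% of participants in each arm | Yes, a small random subset |
| FECC | Purposive interview sample | No |

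Being a subset measure is not the problem, since CCMT is one too. The difference is that CCMT respondents are drawn at random within arm, whereas FECC respondents are selected purposively, partly on a variable that exists in one arm only.

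**2. Size of the FECC sample**

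The interview total reproduces: 20 + 20 + 20 = 60, as stated. Providers do not complete FECC. That leaves 20 caregivers (following Table 5) or up to 20 + 20 = 40 people (following the FECC section, which includes study participants). Assuming one caregiver per participant, 20/440 = 4.5% of caregivers.

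**3. Detectable difference (illustration only)**

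The article gives no split by arm and no power for FECC. Assume an even split, a two-sample t-test at a single time point, two-sided 5% and 80% power. The normal approximation is (1.960 + 0.842) × √(2/n):

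- n = 10 per arm: 2.802 × 0.447 = 1.25 SD; the exact t-based value is 1.32 SD.
- n = 20 per arm: 2.802 × 0.316 = 0.89 SD; the exact value is 0.91 SD.

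The 20 v 20 case treats all 40 respondents as independent, although some may be patient and caregiver pairs. A model using both 6 and 12 months might do somewhat better. The interview section places interviews at 6 months while Table 5 marks 6 and 12, so the number of FECC measurements per person is itself unclear.

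**4. Shift produced by selection alone (illustration only)**

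Assume no true effect, controls unselected, and adherence and FECC jointly normal with correlation ρ in the TtLIVE arm. Take the low stratum as the bottom 20% of adherence and the high stratum as the top 40%. None of these inputs is in the article. Mean standardised adherence is then -1.400 in the low stratum and +0.966 in the high stratum. If a share f of the TtLIVE interviewees are high adherers,

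spurious difference = ρ × [f × 0.966 + (1 - f) × (-1.400)].

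| ρ | f = 0.25 | f = 0.50 | f = 0.75 |
|---|---|---|---|
| 0.2 | -0.16 | -0.04 | +0.07 |
| 0.3 | -0.24 | -0.07 | +0.11 |
| 0.5 | -0.40 | -0.11 | +0.19 |

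A simulation with the same assumptions gave the same range, about -0.40 to +0.19 SD. Both sign and size depend on which adherers happen to be chosen. Table 5 shows no baseline FECC, so baseline FECC cannot be used to adjust for differences between the selected groups.

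**The case against.** **The model may not be an arm comparison.** Section {20a} names no arm term for FECC, and a mixed model can simply describe scores at two times within one sample. This stands as a limit: the contrast is an inference. It is still the likelier reading of a list that includes EQ-5D and Zarit in a parallel-group trial, and nothing in the text excludes it.

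**FECC is an exploratory process measure.** This is correct; no objective or power claim rests on a FECC arm effect. It lowers the consequence but does not make the groups comparable. Process-measure status in fact favours descriptive reporting.

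**The full protocol may settle the detail.** It may well give the interview split by arm, and its absence from the article is no fault. The point is that the sections shown do not fit together as written.

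Three stronger readings are tempting and not supported:

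- A reader might infer that FECC sits in a list of outcomes measured in everyone. CCMT, in the same list, is a 10% subset.
- A reader might infer that FECC is the only quantitative measure of care coordination. CCMT also quantifies coordination, through encounters and time spent.
- A reader might infer that controls are absent or few. The article does not say so; four of the five diversity criteria (diagnosis, ventilation type, site, residence) apply to both arms.

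Low power in a nested sample, or the lack of a baseline FECC, would not by itself be an error.

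**Conclusion.** The point holds in a limited form. The article restricts FECC to a purposive interview sample selected partly on TtLIVE adherence, and then lists it without restriction for the mixed models in {20a}. If that model is used to compare arms, the result is not a randomised comparison, and it cannot be estimated at all if no controls are interviewed.

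The conclusion rests on two things: the natural but unstated reading of {20a} as an arm comparison, and the stated sampling rule. It does not rest on the detectable differences or the simulated shifts, which depend on an arm split and other inputs that the article does not give. The consequence is confined to one exploratory process measure.

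**What to change.** Remove FECC from the mixed-model list in {20a}, and state there that it will be reported descriptively within the interview sample, with no between-arm estimate or p-value. This costs wording only and agrees with the process-measure status in Objectives {7} and Table 4.

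Only if an arm comparison of FECC is wanted would collection have to change, to a random sample within each arm, as already planned for CCMT. That is optional and not cheap: Table 5 puts FECC at 20 to 30 minutes per administration, and the Discussion already names data-collection burden as a challenge.

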##### VentSS

This questionnaire has been developed for this trial to ask questions about ventilator usage and issues as well as clinical signs and symptoms of the study participants. There are a total of 9 questions.

##### S^3^-NIV

We will use an adapted version of this questionnaire to evaluate 3 important domains related to HMV, specifically respiratory symptoms, sleep quality, and ventilation-related side effects, in both invasively and non-invasively ventilated participants. This is a self-administered questionnaire that has demonstrated validity and test-retest reliability for patients using home non-invasive ventilation ^25^.

#### Care coordination measures

##### Care Coordination Measurement Tool (CCMT)

We will use this validated tool to track health care delivery activities [36]. The tool has established validity for children established on HMV [36]. We will use the tool for HMV center/clinic team members to quantify and characterize all VAI care encounters including time spent [37]. We will assess the relationship between these encounters and later resource utilization. The CCMT will be completed for a randomly selected 10% of study participants in each study arm to minimize the documentation burden for healthcare providers.

#### Process measures

For those participants randomized to the intervention arm, we will measure usage metrics and adherence to TtLIVE intervention components. Specifically, we will document:
*n* (%) of the 5 (1, 3, 6, 9, 12 months) clinic visits conducted virtually as opposed to face-to-face*n* (%) of the 5 (1, 3, 6, 9, 12 months) virtual device data downloads available for the HMV team at the virtual clinic visit*n* (%) of participants with a fully completed virtual care plan 6 weeks after study enrolment*n* (%) of the 26 bimonthly symptom/ventilator check-in questionnaires completed (i.e., administered every 2 weeks)*n* (%) of the 12 monthly S^3^-NIV questionnaires completed (i.e., administered monthly)Number of messages, audio calls, and telephone calls initiated by patients/family and healthcare providersNumber of concerning (status yellow and red) ventilator monitoring alerts based on bimonthly and monthly symptom monitoring, and time to alert being addressed.Adverse events unique to the use of the aTouchAway™ platform and the internet.

#### Nested qualitative interviews

We will conduct semi-structured interviews with a purposive diverse sample (ALS versus non-ALS, invasive versus non-invasive ventilation, different study sites, rural versus urban residence, low (< 40%) and high (≥70%) intervention adherence) of 20 VAIs, 20 family caregivers of study participants and 20 circle of care healthcare providers (at 6 months (*n*=60)) to explore barriers and facilitators to intervention adherence.

To participate in interviews, participants or their caregivers must be able to communicate verbally for the duration of an interview. Health care providers must meet the following criteria:

##### Interview inclusion criteria for healthcare providers

Healthcare provider for individuals newly initiated (in-hospital or outpatient) on HMVUse of the aTouchAway™ for at least five participant encountersProvides informed consent.

Once informed consent is obtained, interviews will be conducted by telephone or via audio or video communication on the aTouchAway™ app based on participant preference. All interviews will be conducted by the same study team member with expertise in qualitative interviewing and knowledge of this study population. Using the same interviewer ensures consistency and opportunity to introduce and probe topics raised by other participants. Interviews are expected to last approximately 60 min, will be digitally recorded with permission, and transcribed verbatim by a professional transcription company. We will remove identifying personal information from interview data prior to the analysis of the interview transcripts.

### Participant timeline {13}

The participant timeline is shown in Table 5.

**Table 5 Tab5:** Study participant assessment timeline

Tool	Time	Baseline	Every 4 weeks	Monthly	Any clinical encounter	3 month	6 months	12 months
**Participants (with/without caregiver assistance)**								
Demographic/baseline data	10–15 min	X						
Ambulatory and Home Care Record (Hybrid) [27,28 ]	10–20 min	X	X					
Euro-Quality of Life- 5D-5L Dimensions Scale [32,33] (5D-Y for kids)	10–15 min	X					X	X
Qualitative interviews**	60 min						X	X
S3-NIV*** [6]	5 min	X		X				
Pearlin Self-Mastery Scale	5 min	X				X	X	X
VentSS***			X					
**Caregivers**								
Demographic data	5 min	X						
Qualitative Interviews**	60 min						X	X
Family Experiences with Coordination of Care	20–30 min						X	X
Zarit Burden Interview	5–10 min	X					X	X
**Healthcare providers**								
Care Coordination Measurement Tool	< 5 min				X			
Qualitative interviews**	60 min						X	X

***Only completed by intervention group

**Only completed by a subset of participants/ caregivers/ healthcare providers

*Only completed by caregivers completing qualitative interviews

### Sample size {14}

To determine our sample size we used simulations and data from our previous study of VAIs using Ontario health administrative data [2]. We simulated data based on a negative binomial distribution assuming 50% of VAIs visit the ED and had a mean number of 2.6 visits, for an overall yearly incidence rate of 1.3 ED visits. We need 200 participants/ study group to detect a 30% drop-in yearly incidence rate to of 0.91 at 12 months with *α* = 5% and power 80%. Given an estimated attrition rate of 10%, we will recruit a total of 440 participants. For our co-primary outcome, assuming a minimum clinically important difference in the Pearlin Mastery Scale score of 2.95, standard deviation of 4.5, power of 90%, and alpha = 5%, we would require a sample size of 50 study participants in each group for a total of 100 participants [38, 39]. Therefore, with our planned sample size of 440 participants, we are powered for our co-primary outcomes of ED visits and family caregiver reported Pearlin Mastery Scale score.

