### Trial design {8}

This will be a superiority trial design. This is a pragmatic parallel group (single blind – outcome assessors) randomized controlled trial (NCT04180722) with a nested qualitative evaluation of the 12-month TtLIVE intervention compared to standard of care, with 1:1 allocation of eligible individuals (children and adults) newly transitioning to HMV. The trial was designed in accordance with the established *Standard Protocol Items: Recommendations for Interventional Trials (SPIRIT) guidance* [26]. For participants allocated to the intervention group, the TtLIVE intervention will be delivered through the aTouchAway™ e-platform (via an electronic tablet, Smartphone, or lap/desktop) by a participating specialist HMV program or clinic. For participants allocated to the control group, usual care of their specialist HMV program or clinic will be provided.

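### The sample-size inputs for ED visits give about 60% power at 200 per arm, not the stated 80%

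*Protocol article*

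**What the plan says.** Section Sample size {14} describes the control arm as follows: "We simulated data based on a negative binomial distribution assuming 50% of VAIs visit the ED and had a mean number of 2.6 visits". Multiplying the two figures, it arrives at a control rate of 1.3 per year. The size claim is: "We need 200 participants/ study group to detect a 30% drop-in yearly incidence rate to of 0.91 at 12 months". The claimed power is 80% at a 5% alpha. Sidedness and the dispersion parameter are not given. The inflation step is: "Given an estimated attrition rate of 10%, we will recruit a total of 440 participants". The section separately finds that the Pearlin Mastery score needs 50 per group, and concludes that 440 participants give adequate power for both co-primary outcomes.

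Allocation is 1:1 (Trial design {8}). On analysis, Statistical methods {20a} says: "The number of ED visits will be analyzed using Poisson or negative binomial regression".

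**The concern.** The missing dispersion value is not a detail left to a fuller document. A negative binomial is fully determined by its mean and its share of zeros, and the section gives both: mean 1.3, and half the patients with no visit. The power at 200 per arm can therefore be recomputed from the printed inputs, and it falls well short of 80%.

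ED visits are what make this a 440-patient trial; the Pearlin score alone would need 100. If power for ED visits is overstated, readers will give a non-significant ED result more weight as evidence against a 30% reduction than the design supports.

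**Working it through.** **Inputs (all from Sample size {14} unless noted).** Control rate 1.3 per year (0.5 × 2.6); share with no visit 0.50; intervention rate 0.91 (rate ratio 0.70); 200 per arm; alpha 5%, taken as two-sided because the section does not say; 10% attrition; 440 recruited; 1:1 allocation (Trial design {8}).

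**Step 1: dispersion.** For a negative binomial with mean μ and dispersion k, the variance is μ + kμ² and P(0) = (1 + kμ)^(−1/k). Setting (1 + 1.3k)^(−1/k) = 0.50 gives k = 1.658, a variance-to-mean ratio of 1 + 1.3 × 1.658 = 3.15.

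**Step 2: power at the plan's 200 per arm.** With the same k in both arms:

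- Var(log rate ratio) = [(1/1.3 + 1.658) + (1/0.91 + 1.658)] / 200 = 0.0259, so SE = 0.161
- |ln 0.70| / SE = 0.357 / 0.161 = 2.216
- Power = Φ(2.216 − 1.960) = **60.1%**, against the stated 80%

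**Step 3: other sample sizes, same formula.**

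| Analysable per arm | Two-sided power |
|---|---|
| 198 (220 less 10%) | 59.7% |
| 200 | 60.1% |
| 220 (no loss) | 64.2% |
| 320 | 80.0% |

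Required n per arm for 80% = (1.960 + 0.842)² × (1/1.3 + 1/0.91 + 2 × 1.658) / 0.357² ≈ 320.

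**Step 4: simulation.** In 3,000 simulated trials at 200 per arm with a fitted negative binomial, the Wald test rejected in 60.3% and the likelihood-ratio test in 59.9%. With no true effect (2,000 trials) the Wald test rejected in 5.3%, so the test is sound.

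**Step 5: what would make 200 correct?** Solving Step 2 for 80% power gives k = 0.687. Then P(0) = (1 + 1.3 × 0.687)^(−1/0.687) = 39%, which contradicts the stated 50%.

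**Step 6: other readings at 200 per arm.**

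| Reading | Power |
|---|---|
| Negative binomial, one-sided 5% | 72% |
| Negative binomial, 50% zeros in both arms (k = 0.753 in the intervention arm) | 68% by formula, 66% simulated |
| Zero-inflated Poisson, negative binomial analysis | 52–64% simulated; 73% by variance-matched formula |
| Hurdle with zero-truncated Poisson, visitor share falls to 35% | 69% by formula, 59% simulated |
| Hurdle with zero-truncated Poisson, effect only among visitors | 81% by formula with arm-specific variances, 77% with the control dispersion in both arms, 74% simulated with negative binomial analysis |
| Plain Poisson data | 96% (116 per arm would suffice) |
| Negative binomial data, uncorrected Poisson test | rejects in 86%, but type I error about 27% |

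**Step 7: smallest effect with 80% power (k = 1.658).** Rate ratio 0.65 at 220 per arm and 0.63 at 198 per arm, i.e. a 35–37% reduction.

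**Step 8: attrition.** 440 × 0.9 = 396, not 400; 400 / 0.9 = 444.4, so 445. This costs less than half a percentage point of power.

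**Pearlin score.** A difference of 2.95, SD 4.5 and 90% power give 49 per arm against the stated 50. That figure stands.

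**The case against.** The strongest reply is that the section does not say outright that the zero probability of the negative binomial was set to 0.50. It gives a visiting share and a mean among visitors, and says the simulation drew on a previous study. A two-part simulation could fit that wording. If half of each arm visits and visitors follow a zero-truncated Poisson with means 2.6 and 1.82, a variance formula gives 81% at 200 per arm, close to the stated figure.

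That possibility is real, but it does not rescue the text. The model is not a negative binomial, which the section names. It needs the whole effect to fall on repeat visits, with nobody's first visit prevented, which the section never says. Under the negative binomial regression that {20a} allows, its simulated power is 74%. If this is what was simulated, the description is wrong and still needs correcting.

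Unstated sidedness does not help either: one-sided 5% gives 72%.

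Three parts of the objection stand. The attrition slip is small, and because ED visits come from linked provincial data, questionnaire dropout need not lose the outcome; that is why 220 per arm is shown as the favourable case. Shorter follow-up through death would lower power, but the documents do not allow this to be sized, so no figure here depends on it. And the protocol sets no rule for reading a null result, so over-reading is a risk rather than a stated plan.

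**Conclusion.** The concern holds. On the section's own inputs, power for a 30% reduction in ED visits is about 60% at 200 or 198 per arm and at most 64% with complete data on 440. The stated 80% would need about 320 per arm, or a dispersion that contradicts the stated 50% of visitors.

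This assumes a two-sided 5% test, a common dispersion in both arms, a full year of follow-up, and that the 50% and 1.3 describe a single negative binomial. The 60% figure is firm, by formula and by simulation. The figures for other models vary with the method, but among two-sided readings with a valid test, only the hurdle with the effect confined to visitors approaches 80%; plain Poisson exceeds it by discarding the stated overdispersion. Because this outcome sets the trial's size and the section says it is adequately powered, the statement must be corrected.

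**What to change.** Amend Sample size {14}; no patients need be added.

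- State the simulation model, the dispersion in each arm and whether the test is two-sided.
- If the model was the negative binomial described, replace the power statement with, for example: with 440 randomised (198 to 220 analysable per arm), power for a 30% reduction in the ED visit rate is about 60–64% at two-sided 5%; the trial has 80% power for a reduction of 35–37%.
- If another model was simulated, describe it, including where the effect acts, and report the power obtained under the planned regression.
- Limit the closing claim of adequate power to the Pearlin score unless 80% can be reproduced for ED visits.
- Correct the attrition step: 440 less 10% leaves 396; 400 analysable needs 445.

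The cost is protocol wording and a less favourable stated power. Design, data collection and analysis are unchanged.
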